**Methods:**

A national multicentre, register-based, randomised controlled trial (rRCT) will be conducted. For this trial, 1440 patients, ≥75 years with an acute uFNF, will be allocated. Eligible patients will be identified by the Swedish Fracture Register (SFR) platform, which will notify the admitting orthopaedic surgeon of eligibility. After informed consent has been given and documented, patients will be randomised to either IF (control group) or arthroplasty (intervention group) within the SFR platform. Injury mechanism, fracture classification, date of injury, and type of treatment are registered in the SFR. Type and brand of arthroplasty, surgical approach, and fixation are obtained from the Swedish Hip Arthroplasty Register (SHAR). The study cohort from the SFR will be cross-checked with the National Patient Register and the SHAR for outcome variables at 2, 5, and 10 years.

The primary outcome will be a composite variable comprising reoperation rate and mortality at 2 years postoperatively. Secondary endpoints will include reoperation rate and mortality as stand-alone variables. In addition, secondary endpoints will be patient-reported outcomes as measured by the Short Musculoskeletal Functional Assessment questionnaire at 1 year postoperatively as routinely collected within the SFR. Further secondary endpoints will include the occurrence of adverse events such as pneumonia, stroke or myocardial infarction and evaluation of the external validity of the study.

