### Aim

This study will aim to compare IF and hip arthroplasty for uFNF in the older patient using a composite variable consisting of reoperation rate and mortality. Patient-reported outcome measures (PROMs) and the frequency of adverse events will also be assessed.

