#### Secondary endpoints

Secondary endpoints will include reoperation rate and mortality as stand-alone variables.

PROM, as measured by the Short Musculoskeletal Functional Assessment (SMFA) questionnaire [15], will be routinely collected within the SFR 1 year after the injury and compared with the results obtained by recall technique at the time of the fracture. No additional PROMs will be collected.

Other secondary endpoints will include the occurrence of adverse events defined as suffering, physical harm or disease, as well as death related to the index admission and as a condition that was not an inevitable consequence of the patient’s disease or treatment. The external validity of the trial will be evaluated by comparing the outcome between those who were included in the rRCT with those who fulfilled the inclusion criteria but declined to participate.

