### Data collection and follow-up

Data on baseline characteristics and outcome variables are registered in the NPR, SHAR, and SFR. Follow-up will be performed postoperatively after 2, 5, and 10 years by linking between the registers (Table 1).

**Table 1 Tab1:** Content for the schedule of enrolment, interventions, and assessments

TIMEPOINT	STUDY PERIOD				
	Enrolment	Allocation	Post-allocation		
	*0*	0	*2y*	*5y*	*10y*
ENROLMENT:					
Eligibility screen	X				
Informed consent	X				
Randomization		X			
INTERVENTIONS:					
*Internal Fixation (control)*		X			
*Hip Arthroplasty (intervention)*		X			
ASSESSMENTS:					
*Baseline*	X	X			
*Primary outcome*			X	X	X
*Secondary outcome*			X	X	X

Primary outcome is a composite variable of reoperation rate and mortality

Secondary outcomes are: Reoperation rate, Mortality, PROM, Adverse Events, External validity

All outcomes will come from Registers

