### Estimated sample size and power

The reoperation rate for hemiarthroplasty due to FNF is estimated at 5% according to reports from the SHAR [16, 17]. In recent registry based studies, patients with an FNF treated with THA had a significantly reduced risk of reoperation when compared with patients treated with hemiarthroplasty [18, 19]. Because we know that the variable “reoperations” does not have 100% completeness in the SHAR given that some procedures (e.g., debridement and irrigation or closed reduction) are not reliably registered, we assume that the actual reoperation rate is closer to 7.5%. The reported reoperation rates for uFNFs vary [6, 7, 20, 21], but we estimate that the rate is about 12.5% at 1 year after IF with screws/pins in older patients with uFNF. Mortality rates are reported from 11% at 1 year in a study with both displaced and undisplaced FNFs [22] to just over 20% in other studies [6, 8, 21].

In our primary outcome composite variable (reoperation rate and mortality), we expect a 15% 1-year mortality within the study cohort. We assume that death or reoperation would occur within 1 year in 27.5% (15% + 12.5%) of the patients in the control group (IF) and aim to detect a decrease to 22.5% (15% + 7.5%) in the intervention group (arthroplasty). We plan to include patients for 3 years. Patients will be censored at the time of reoperation or at time of death within 2 years, at time of withdrawal of informed consent or at the end of the study. The end of study will be when the last patient has a 1-year follow-up, cross-checking with the NPR has a 1 year delay for data completeness; hence, about two thirds of the patients will have a 2-year follow-up and the remaining patients between 1 and 2 years. Simulations under an assumption of constant hazard indicate that 1440 patients enrolled for 3 years, yielding about 586 events, would produce a power of 80% to detect such a difference. The analyses were performed using R v. 3.3.1 and the survival package v. 2.39.4.

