### Statistics

Time to first event will be presented as Kaplan-Meier plots. The primary composite and the individual components will be analysed for time to first event using Cox regression adjusted for age as a linear covariate and presented as hazard ratios with 95% confidence intervals and *p*-value. Because of the register follow-up, we assume that follow-up will be complete. In the rare event that a patient is known to have incomplete follow-up, the patient will be considered censored at the last known follow-up. For the reoperation endpoint, death will be handled as censoring events.

The number of patients with a perioperative event and event within 2 years will be summarised in tables. Patients lost to follow-up will be included in the denominator, and the 2-year frequencies will only include patients randomised at least 2 years before data collection. Supplementary sensitivity analyses will include analyses censored at 1 year and analyses of the number of patients with events within 2 years. Secondary outcomes will be presented in the same way as the primary composite and its components.

Statistical expertise at the Uppsala Clinical Research Center will perform the statistical analyses. Data will be blinded for the principal investigators until the final analysis has been performed and until the writing of the manuscript.

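### The blanket rule for secondary outcomes gives the 1-year SMFA score a time-to-event presentation that cannot apply to it, and no comparison of SMFA between the arms is named

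*Protocol article*

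**What the plan says.** The Statistics section defines the presentation of the primary outcome. "Time to first event will be presented as Kaplan-Meier plots", and the composite and its components are "analysed for time to first event using Cox regression adjusted for age as a linear covariate and presented as hazard ratios with 95% confidence intervals"; a p-value is also reported. Tables of patients with events are added. The section's rule for everything else is one sentence: "Secondary outcomes will be presented in the same way as the primary composite and its components". It makes no exception.

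SMFA falls under that rule. The abstract states that "secondary endpoints will be patient-reported outcomes as measured by the Short Musculoskeletal Functional Assessment questionnaire at 1 year postoperatively", and the note under Table 1 reads "Secondary outcomes are: Reoperation rate, Mortality, PROM, Adverse Events, External validity".

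The Secondary endpoints section says that the 1-year SMFA will be "compared with the results obtained by recall technique at the time of the fracture". It adds that no other patient-reported measure will be collected. The Aim section sets out to compare internal fixation with hip arthroplasty and continues: "Patient-reported outcome measures (PROMs) and the frequency of adverse events will also be assessed".

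**The concern.** The rule suits reoperation and mortality, and event counts can suit adverse events. It does not suit a score. A Kaplan-Meier curve, a hazard ratio and a count of patients with an event all need an event, and SMFA at 1 year has none. This is a method stated wrongly for one endpoint, not a detail left to a later document: an analysis plan that treated SMFA sensibly would have to depart from the published sentence.

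The one SMFA comparison that is spelled out for the treated patients sets each patient against their own recalled state. Taken alone, that is not a randomised comparison and does not inform the choice between the two operations.

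SMFA is the trial's only patient-reported evidence, and treatment is not blinded. With the contrast unnamed, the raw 1-year score, the change from recall and the baseline-adjusted score all remain open choices. They differ in precision and can give different estimates.

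**Working it through.** **1. Does the stated method fit the endpoint?**

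| Element of the rule (Statistics) | What it needs | What SMFA has |
|---|---|---|
| Kaplan-Meier plot | time to first event | one score at 1 year |
| Cox hazard ratio | event times and censoring | none |
| Table of patients with an event | a defined event | none |
| Censoring at last known follow-up | follow-up time | no meaning for a score |

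No element applies. The carry-forward rule in the section on withdrawal does not help either, because SMFA has only one measurement after baseline.

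**2. Is a comparison of SMFA between arms named anywhere?** The Secondary endpoints section names a comparison with recall. The Discussion names a comparison of patient-reported outcomes between participants, those who declined and those eligible but not screened. Neither sets internal fixation against arthroplasty. The Aim implies such a comparison but does not specify it.

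**3. How many patients can contribute a score?** The sample-size section states "we expect a 15% 1-year mortality within the study cohort", and the planned size is 1440.

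- Deaths by 1 year: 0.15 × 1440 = 216.
- Alive at 1 year: 0.85 × 1440 = 1224.

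This is an upper limit, because no questionnaire response rate is given.

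**4. How much does the choice of contrast matter?** The documents give no SMFA effect size, standard deviation or correlation, so only relative variances can be shown. Let r be the correlation between recalled and 1-year SMFA, with equal variances at the two times. Relative to an unadjusted comparison of 1-year scores (variance 1), a change score has 2(1 − r) and a baseline-adjusted analysis has 1 − r². The range 0.4 to 0.6 for r is an assumption.

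| r | Unadjusted | Change score 2(1 − r) | Adjusted 1 − r² | Adjusted vs unadjusted | Adjusted vs change score |
|---|---|---|---|---|---|
| 0.4 | 1 | 1.20 | 0.84 | 16% lower | 1 − 0.84/1.20 = 30% lower |
| 0.6 | 1 | 0.80 | 0.64 | 36% lower | 1 − 0.64/0.80 = 20% lower |

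**5. Is the primary analysis touched?** No. There is no SMFA figure in the plan to reproduce, but the primary figures do reproduce. Under constant hazards, 1-year risks of 27.5% and 22.5% give HR = ln(1 − 0.225)/ln(1 − 0.275) = 0.793. With 720 patients per arm, uniform 3-year accrual, an end 1 year after the last patient and a 2-year cap, about 586.4 events are expected (586 stated). Schoenfeld's formula then gives 80.3% power (80% stated), assuming two-sided 0.05 and 1:1 allocation.

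**The case against.** The strongest reply is that the sentence is a loose blanket statement in a condensed article, that it concerns presentation and not analysis, and that the model for a continuous secondary outcome normally sits in an analysis plan, which is not shown. Part of this stands: leaving out covariates, missing-data handling or a sensitivity analysis would be no finding by itself. But the article does not leave the matter open. It states a rule that covers SMFA. The choice of verb does not rescue it either, since the same section uses that verb for the Kaplan-Meier plots and hazard ratios.

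A reader might infer three stronger points that the documents do not support.

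- **That the plan can yield no valid comparison of SMFA between arms.** A comparison with recall also describes a change from baseline, which can be contrasted by arm, as can a 1-year score adjusted for recall. The text leaves this unstated but does not forbid it.
- **That Table 1 contradicts the 1-year time point because it has columns only at 2, 5 and 10 years.** The text introduces those times as register linkages, and a 1-year score held in the fracture register would be available at the 2-year linkage. A 1-year column would be a clerical improvement.
- **That a before-after comparison would show decline in both arms.** Nothing in the documents says so.

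It is also fair to say that the variance figures show the gain from the recommended model, not harm done by the sentence in the Statistics section.

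**Conclusion.** The point holds in limited form. The rule for secondary outcomes cannot be applied to SMFA, and the article names no contrast of SMFA between internal fixation and arthroplasty. Both follow from the text and need no assumption.

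The effect is confined to one secondary outcome, though it is the only patient-reported one. The ceiling of about 1224 scores rests on the protocol's 15% mortality, and non-response would lower it by an unknown amount. The variance gains rest on the assumed correlation and on equal variances. The primary analysis, its power and the event-type secondary outcomes stand as written. The text should be corrected, but the trial's main conclusion does not depend on it.

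**What to change.** Exempt SMFA from the sentence on secondary outcomes, and state that:

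- 1-year SMFA is compared between randomised arms by linear regression, adjusted for recalled baseline SMFA and age;
- the result is an adjusted mean difference with a 95% confidence interval;
- the analysed group is patients alive and responding at 1 year, with the numbers dead and not responding shown by arm.

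The last item matters because the protocol itself allows that arthroplasty might affect mortality, in which case survivors in the two arms need not be comparable. A sensitivity analysis that takes deaths into account is optional.

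The cost is a few sentences and one standard regression. The recalled score, the 1-year score and age are already to be collected, so no new data, visits or patients are needed.

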### Ethics and dissemination

The study will be conducted in accordance with the ethical principles of the Declaration of Helsinki. The study has been approved by the Swedish Ethical Review Authority (Dnr: 2019–00140). Any protocol amendments will be approved by the Swedish Ethical Review Authority and published at www.clinicaltrials.gov (NCT03966716). The first results from the study will be circulated to the medical community through presentations and publications in a scientific, peer-reviewed, open access medical journal.

## Discussion

The present trial will provide improved evidence for the future choice of treatment for patients with Garden 1–2 FNF who are ≥75 years old.

Patients with dementia represent a large proportion of the hip fracture population but the inclusion of this group is difficult because of the need of informed consent by next of kin (or power of attorney) and thus exposes the study for inclusion bias. Informed consent has been constructed in two versions, one for lucid patients and one for patients with cognitive impairment not able to give informed consent; the latter version allows us to address next of kin. There is a national effort in Sweden to treat hip fractures within 24 h of admission and with operative intervention performed only during duty hours, the recruitment process is difficult, which could result in selection bias. The Garden classification does not take into account posterior or anterior fracture tilt. There are reports discussing the linkage of posterior and anterior tilt to failure after IF, a situation that might lead to reluctance to include these patients in this study [20, 21, 23–25].

The primary endpoint, defined as a composite variable (reoperation rate and mortality), is constructed to consider both mortality and reoperations. A longer and more strenuous initial procedure (i.e. arthroplasty) might affect peri- and postoperative mortality and thus mask potential reoperations. However, a recent RCT comparing hemiarthroplasty and IF in patients with uFNF reported a higher mortality rate after IF [8].

The external validity of the trial will be evaluated by comparing mortality, complications, and PROM between those who were included in the rRCT, those who fulfil the inclusion criteria for the rRCT trial but declined participation, and those eligible but not screened. The limitations of the present trial include the lack of blinding of surgeons and patients, the potential of randomisation bias because the two compared procedures (IF, arthroplasty) differ in complexity, required surgeon skills, and duration. The strengths of the study are the pragmatic rRCT study design that includes a national coverage of hospitals, a large sample size, and clinically relevant outcomes. The results from the study will be dispersed to the medical community by way of presentations and publications in relevant medical journals.

## Data Availability

The datasets used during the current study are not publicly available because of patient integrity but are available from the corresponding author on reasonable request.

## Abbreviations

IF: internal fixation
NPR: National Patient Register
PROMs: patient-reported outcome measures
rRCT: register-based randomised controlled trial
SFR: Swedish Fracture Register
SHAR: Swedish Hip Arthroplasty Register
SMFA: Short Musculoskeletal Functional Assessment questionnaire
uFNF: undisplaced femoral neck fracture
